### Procedure

Prior to completing the survey, eligible NSCLC participants will be provided with a Participant Information Sheet containing the goals of the study, expectations for participation, and contact information of the study team by a nurse, a clinician, or a researcher. Eligible participants will receive a personalized link to the online survey. Only participants who provide their informed consent as part of the survey will be able to complete the online survey. The survey will be administered by Sawtooth software v.9.9.2 offered *via* a server of Uppsala University.

A first version of the survey will be pretested in a small group of five patients by means of think-aloud interviews. These patients will provide feedback on the survey to make sure that it is understandable and is not too time consuming or burdensome. The tool content and format will be revised in response to this feedback.

The study will be conducted in compliance with the EU General Data Protection Regulation (GDPR) and all other European and national legislations. Additionally, this study was approved by the Ethical Committee of the European Institute of Oncology IRCCS (IEO, Milan, Italy; reference R1142/20-IEO 1206) and the “Ethische Commissie Onderzoek UZ/KU Leuven” (Belgium; reference S64022).

### Participants

The study aims to recruit 510 NSCLC patients from three cancer treatment centers (*N* = 170 per center) in Italy (*N* = 340) and Belgium (*N* = 170). Italian patients will be recruited at the European Institute of Oncology and the National Institute of Cancer in Milan. Belgian patients will be recruited at the Respiratory Oncology Department and the Department of Thoracic Surgery of the KU Leuven University Hospital in Leuven. Each cancer center treats approximately 500 NSCLC patients yearly. NSCLC patients in different stages (stages I–IV) will be recruited and divided into two groups (see Figure 1): 255 early stages (stages I and II) and 255 later stages (stages III and IV).

**Figure 1 F1:**
[figure not shown]
Targeted sample distribution. NSCLC, non-small cell lung cancer; IEO, European Institute of Oncology; INT, National Institute of Cancer; KU Leuven, KU Leuven University Hospital in Leuven; Early, early stages (I–II); Late, late stages (III–IV); DCE, discrete choice experiment; SW, swing weighting.

Treatment options for patients, their prognosis, and their perception of the disease widely differ according to the stage of LC. The treatment attributes included in the study could be more familiar or realistic for late-stage LC patients at the time of their participation. However, we include both early- and late-stage patients since the hypothetical scenarios presented would be relevant to both groups; some of the early-stage patients could, in the future, be confronted with the same therapy choices as patients in later stages. In addition, one of the aims of this study is to investigate whether disease stage, alongside other clinical variables (i.e., line of treatment), socio-demographic (i.e., age, gender, and educational level), and psychological characteristics of the patients (i.e., health literacy and health locus of control), would be related to PP heterogeneity. Table 1 shows participants' inclusion and exclusion criteria.

**Table 1 T1:** Inclusion and exclusion criteria.

**Inclusion criteria**	**Exclusion criteria**
NSCLC patients	Inability to consent or assent by themselves
I–IV stages of lung cancer	Aged < 18
Aged ≥ 18	Inability to read, speak, and understand either Italian or Dutch
Able to give informed consent	
Able to read, speak, and understand either Italian or Dutch	

### Sample Size Estimation

For SW, no specific sample size is required since the sample size does not depend on the magnitudes of the utility differences (22). Therefore, the sample sizes will be dictated by requirements for the DCE. To the best of our knowledge, there are no statistical tools able to estimate the sample size for a DCE. Therefore, we referred to the literature to estimate the sample size for the present research. Most published choice experiments have a sample size of between 100 to 300 respondents (23). However, according to Bekker-Grob et al. (24), the minimum sample size depends on several criteria, including the question format, the complexity of the choice task, the desired precision of the results, and the need to conduct subgroup analyses (25, 26). Given this, we have determined that, based on the sample size requirements for both methods and taking into account the number of research questions this study anticipates to answer, a sample size of 510 respondents (170 per site) is expected to provide enough information to identify preferences in each country and comparisons across countries and disease groups with acceptable precision.

### Measures and Development of Preference Elicitation Tasks

The order of the questions in the online survey is shown in Figure 2.

**Figure 2 F2:**

Order of the questions in the survey. DCE, discrete choice experiment; SW, swing weighting.

Socio-demo questions on gender, age, education, relationship status, history of LC in the family, age of the diagnosis of LC, types and number of lines of treatments received, participation in clinical trials, contact with other patients, or patient organizations will be asked. Patients' health-related quality of life will be assessed using the five-level EQ-5D version [EQ-5D-5L; (27)] which comprises five dimensions: mobility, self-care, usual activities, pain/discomfort, and anxiety/depression. The measurement of health-related quality of life and socio-demographic and clinical variables will allow a more precise characterization of patients.

#### Attributes and Levels Development

The selection of the attributes and levels of the DCE and the SW arise from a previous qualitative study (28, 29). Through focus-group discussions conducted in Belgium and in Italy, patients highlighted themes reflecting positive effects, or expected gains of treatment, and negative effects or adverse events that negatively impacted their daily functioning. Twenty-one themes emerged from those discussions, mainly consistent among patients from Belgium and Italy (29).

Two additional focus groups, one in Belgium and one in Italy, were conducted with 13 NSCLC stage III and IV patients (age range 48–70: *M* = 58, *SD* = 7.1; 54% men; *N* = 7 in Belgium; *N*= 6 in Italy). Results were used to derive attributes and attribute levels. From the 21 themes that emerged during the first round of discussions with patients (29), participants selected and rank-ordered the most important ones. The four most important positive characteristics were greater life expectancy, decrease in cancer growth, cancer remission, and the maintenance of daily functioning, and eight most important negative characteristics were severity of skin problems, nausea, serious infections, hair loss, and infusion reactions, gravity of fatigue, probability of renal failure, and probability of cognitive limitation.

Multi-stakeholder discussions involving clinicians and preference research experts were then organized to further discuss the characteristics and define the final attributes, their associated levels, and their explanations. For parsimony and to avoid overlapping categories, the three categories greater life expectancy, decrease in cancer growth, and remission were combined into “chance to be alive at least 5 years after the initiation of the therapy.” The category of maintenance of daily functioning was renamed as “chance to carry out activities of daily living” (e.g., social interaction, working productivity, household activities, practice sports, being able to go on holiday). Therefore, the list that was evaluated by three clinicians (two in Italy and one in Belgium) comprised two positive characteristics (i.e., the probability of >5 years of survival and chance to carry out activities of daily living) and nine negative characteristics (i.e., severity of skin problems, nausea, serious infections, hair loss, and infusion reactions, gravity of fatigue, probability of renal failure, and probability of cognitive limitation).

The multi-stakeholder discussions resulted in the deletion of four characteristics: the severity of infections, severity of infusion reactions, probability of cognitive limitations, and probability of renal failure. All those characteristics were deleted because according to the clinicians they are deemed as rare in NCSLC. The severity of the nausea was deleted because it can be treated and controlled by other existing drugs. Since attributes should be unambiguous, clear, tradable, and distinctly different from other included attributes (30), the chance to carry out activities of daily living was deleted from the list because (a) it is difficult to find a univocal definition for that feature, (b) it overlaps with the other included attributes (it is an overarching theme encompassing the other, more specific, attributes), and (c) it may be interpreted differently by different patients. The attribute of treatment modality (i.e., how the treatment is given to you) was added because it differs across different treatments that have been developed for NSCLC and knowing whether this attribute actually influences patients' decisions could be valuable information in HTA and regulatory decisions. The final list is composed of five attributes with three levels each (see Table 2). The same attributes and levels have been implemented in both DCE and SW to allow for their comparison.

**Table 2 T2:** Attributes, definitions, and levels.

**Attribute**	**Definition**	**Levels**
How the treatment is given to you	How the cancer treatment is given to you and the length of time each treatment takes.	This can either be: - Infusion (injection administered into your veins) that requires a hospital stay of 1 day (about 24 h) - Infusion (injection administered into your veins) that requires a hospital stay of half a day (about 12 h) - Oral treatment (by swallowing), and no hospital stay is required
Chance of surviving 5 years after starting this cancer treatment	The chance of still being alive 5 years after starting this cancer treatment	This chance can either be: - 10%—meaning that 10 people out of 100 people that started the treatment are still alive after 5 years, and 90 people died within those 5 years - 20%—meaning that 20 people out of 100 people that started the treatment are still alive after 5 years, and 80 people died within those 5 years - 40%—meaning that 40 people out of 100 people that started the treatment are still alive after 5 years, and 60 people died within those 5 years
Chance of long-lasting skin problems	The chance that skin problems occur after treatment. This skin problem lasts at least a month and could be a rash, severe itching, bleeding, and/or dryness	This chance can either be: - 10% (10 out of 100)^a^ - 20% (20 out of 100)^a^ - 40% (40 out of 100)^a^
Chance of being extremely tired	This refers to feeling completely exhausted and lacking energy even after limited activities. It lasts as long as the treatment takes to be administered.	This chance can either be: - 10% (10 out of 100)^a^ - 40% (40 out of 100)^a^ - 60% or (60 out of 100)^a^
Severity of hair loss	The type and amount of hair loss. It lasts as long as the treatment takes to be administered.	This can either be: - No hair loss - Weakening/thinning of hair - Complete loss of hair

a *The percentage is presented also in a graphical form displaying 100 stylized human figures and highlighting a number of them with a color corresponding to the given percentage*.

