Nevertheless, without clinical trials comparing different NSCLC treatment options, there is no clinical evidence that allows to determine a clinically superior treatment for advanced stage patients. Further, NSCLC treatments (including immunotherapy and chemo-immunotherapy) have different treatment characteristics that may influence treatment decisions. NSCLC treatments vary in terms of mode of administration, treatment schedules, and benefit–risk profiles. For instance, while chemo-immunotherapy is administered as an intravenous infusion lasting at least 4–5 h, immunotherapy has a much shorter infusion time of about 1 h. Toxicity profiles also differ between NSCLC treatments. For example, chemotherapy can carry both acute and late toxicities; while the former includes nausea, vomiting, paresthesia, anemia, fatigue, and fever, the latter can include persistent neurotoxicity and infertility. However, immunotherapy is typically better tolerated, as the most common side effects are rash, itch, mild diarrhea, fatigue, and subclinical thyroid dysfunction. Therefore, in view of the existence of multiple treatments with varying modes of administration, treatment schedules, benefit–risk profiles, no clinical superior treatment, and treatment options that vary widely according to disease stage and severity (9), PP may play a pivotal role in understanding the relative value of different therapeutic options and their attributes for NSCLC patients. Decisions concerning NSCLC treatment can be considered a PP-sensitive decision, and a better understanding of the patient's experience with NSCLC is therefore pivotal in these circumstances. For example, NSCLC patients have a low life expectancy that varies according to the disease stage (10), and the understanding of their preference regarding treatment options, the maximum acceptable risk (MAR), and the minimum acceptable benefit (MAB) they would be willing to accept for treatment alternatives may inform stakeholders.

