#### DCE and SW Task Construction

The DCE (15) is a quantitative method to assess PP by asking respondents to state their choice over sets of hypothetical alternatives defined by combinations of different levels of several characteristics, hence the attributes. In the present research, respondents will be presented 12 choice tasks, following ISPOR guidelines. Each choice task consists of selecting between two alternative options which describe a hypothetical treatment A and treatment B (see Table 3 for an example of choice task). In each treatment, the five established attributes are linked to one of the three possible levels.

**Table 3 T3:** Example of a DCE choice task created for the study.

	**Treatment A**	**Treatment B**
How the treatment is given to you	Intravenous infusion lasting 24 h	Intravenous infusion lasting 12 h
Chance of survival 5 years after starting this cancer treatment	10% (10 out of 100)	10% (10 out of 100)
Chance of long-lasting skin problems	40% (40 out of 100)	10% (10 out of 100)
Chance of being extremely tired	60% (60 out of 100)	10% (10 out of 100)
Severity of hair loss	Weakening/thinning	No hair loss

NGene 1.2.1 software (31) will be used to create a Bayesian D-efficient design. Prior information used to generate this design was based on the previous literature and best guesses for the pilot study, and outcomes of initial analysis (conditional logit) of pilot data for the main survey. Dominant alternatives where one alternative is clearly “better” than the other alternative were excluded from the design. For both the pilot and the final design, a total of 36 unique choice tasks were generated, which were divided over three blocks; each choice task was assigned to only one of the blocks (each patient answered only 12 choice tasks). Patients will be randomized to either one of the blocks. Interactions between 5-year survival and risk or extreme tiredness, 5-year survival and risk of skin problems, and 5-year survival and mode of administration were included in the design.

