**How the treatment is given to you**	
Intravenous infusion lasting 24 h → oral treatment (pill swallowing)	
	Drag the least important improvement here

Participants will then be asked to assign points to each attribute they have ranked in the previous step. The first attribute automatically receives 100 points; participants have to assign points to all the other attributes (i.e., “weighting”). See Table 5.

**Table 5 T5:** Example of the SW choice task—point allocation.

The improvement of the following characteristic was found to be the most important for you:

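### The infusion levels of the administration attribute are a length of hospital stay in Table 2 but a length of infusion in the example DCE and SW tasks

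*Protocol article*

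**What the plan says.** Table 2 (Attributes and Levels Development) defines the attribute as "How the cancer treatment is given to you and the length of time each treatment takes". The first of its three levels is "Infusion (injection administered into your veins) that requires a hospital stay of 1 day (about 24 h"). The second level in the table reads "Infusion (injection administered into your veins) that requires a hospital stay of half a day (about 12 h"). The third and last level is given as "Oral treatment (by swallowing), and no hospital stay is required".

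The text just before Table 2 refers to it for the five attributes and their levels, and says the same ones are used in both methods so that the methods can be compared.

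Under DCE and SW Task Construction, the example DCE task (Table 3) sets "Intravenous infusion lasting 24 h" against "Intravenous infusion lasting 12 h". The example SW ranking (Table 4) shows the swing "Intravenous infusion lasting 24 h → oral treatment (pill swallowing").

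The Design and Education Tool sections say that patients receive a description of the attributes before the tasks, and that one video explains the attributes and their levels.

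**The concern.** An infusion that requires a day in hospital and an infusion that itself runs for a day are not the same burden. A respondent may weigh the first as time away from home and the second as time attached to a drip. If the description uses one and the task the other, some respondents may answer on the stay and others on the infusion, and the analysis cannot separate them.

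This matters because the attribute was added deliberately, as information for HTA and regulatory decisions. To use the result, a decision-maker has to know what the respondents were trading. The article also sets its own standard for attributes: they should be unambiguous, and daily functioning was dropped partly because patients might read it in different ways. As printed, the administration attribute has the same weakness.

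**Working it through.** The article gives no figure to reproduce, so the check is a comparison of the wording.

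**1. The levels side by side**

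| Place | Worst level | Middle level | Best level | What the hours measure |
|---|---|---|---|---|
| Table 2 | infusion with a stay of about 24 h | infusion with a stay of about 12 h | oral, no stay | time in hospital |
| Table 3 (DCE example) | infusion of 24 h | infusion of 12 h | not shown | time on the infusion |
| Table 4 (SW example) | infusion of 24 h | not shown, as the swing runs from worst to best | oral | time on the infusion |

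The numbers of hours agree wherever they appear. The quantity does not. The definition column of Table 2 does not settle it, because the time a treatment takes can be read either way.

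**2. Does the article treat the two quantities as the same?** No. The Introduction uses infusion time as a quantity of its own: it says "immunotherapy has a much shorter infusion time of about 1 h" and gives at least 4–5 h for chemo-immunotherapy. Nothing elsewhere equates infusion time with length of stay.

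**3. What depends on the level wording.** Under Statistical Analyses, the DCE yields attribute-level estimates and conditional relative importance, and the SW yields a weight per attribute. The DCE design also includes an interaction between 5-year survival and mode of administration. All four quantities take their meaning from what the administration levels say.

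**4. What does not depend on it, or only indirectly.** Tables 3 and 4 share the infusion-time wording, so the mismatch with Table 2 does not by itself separate the two methods. The MAR and MAB concern benefits and risks, so administration could enter them only through the interaction with survival.

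**5. Conditional arithmetic, valid only if the hours are infusion time.** Worst level against the Introduction's durations: 24/5 = 4.8 and 24/4 = 6.0 for chemo-immunotherapy, and 24/1 = 24 for immunotherapy. Because the article says at least 4–5 h, the 4.8 to 6.0 ratios are upper limits. The quoted figures of 1 h and 4–5 h all lie below the shortest infusion level, 12 h. Valuing that contrast from the 12 h and 24 h levels would be extrapolation. If the hours are hospital stay, these ratios do not apply.

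**The case against.** The strongest reply is that this is shorthand in an article. Tables 3 and 4 are labelled as examples, and they reword other levels too, such as the hair-loss categories. Table 3 is also weak evidence of what was fielded: treatment B is better on four attributes and equal on survival, although the article says tasks with a dominant alternative were excluded. The video script and survey screens are not shown. The five-patient think-aloud pretest and the pilot might catch the problem.

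Much of this stands. A reader might infer that patients are taught one thing and then choose on another, but the article does not show that. It shows that its only list of levels and its only two task examples disagree. Rewording a hair-loss category leaves its meaning intact, whereas here the quantity changes. The pretest is a good place to check the wording, but the article does not say that it will address this point.

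Two further readings are tempting and unsupported:

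- **That the harsher task wording inflates this attribute and lowers the apparent importance of survival and toxicity.** Nothing shows inflation or its direction. SW weights come from ranks by the rank order centroid method, so a respondent's weights move only if that respondent's ranking changes.
- **That the levels miss the contrast the attribute was meant to capture.** The Introduction gives the infusion times only as an illustration. The stated reason for adding the attribute is that modality differs across treatments, and the levels include oral treatment.

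**Conclusion.** The inconsistency is in the current text and nothing in the article resolves it. As written, the administration estimate, its relative importance, its SW weight and its interaction with survival cannot be given one meaning. It should be corrected, but it does not invalidate the study: it concerns one of five attributes, does not by itself bias the DCE–SW comparison, and has no bias of known direction or size.

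The conclusion assumes that Table 2 is the basis for the description given to patients and that Tables 3 and 4 reflect the task wording. Both are reasonable, since Table 2 is the only stated list and Table 3 is captioned as a task made for this study, but neither can be confirmed from the article. If the fielded screens already use one wording throughout, what remains is a correction to the published tables.

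**What to change.** - Reconcile Tables 2, 3 and 4 so that one identical level wording appears in the attribute description, the video, the DCE tasks and the SW tasks. Whether it is hospital stay or infusion time is for the study team to decide. Align the definition column of Table 2 with that choice.
- In the think-aloud pretest, ask patients to say in their own words what the 24 h and 12 h refer to.
- If data were already collected, report the fielded wording and interpret the attribute only in those terms. If that wording is infusion time, do not use the 12 h and 24 h levels to value the Introduction's contrast of about 1 h against at least 4–5 h without stating that this is extrapolation.

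Before launch, the cost is text edits to the survey and video, and the experimental design stays as it is. Changing the hours themselves would be a larger step: it would alter the attribute levels and call into question the pilot-based priors behind the Bayesian D-efficient design. Aligning the wording does not require it.

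### Table 2 words the duration of tiredness and hair loss so that it can be read as depending on the mode-of-administration attribute; the mode attribute itself is also worded in two ways

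*Protocol article*

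**What the plan says.** Table 2 (Attributes and Levels Development) gives five attributes with three levels each.

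- **Mode** is defined as "How the cancer treatment is given to you and the length of time each treatment takes". Two levels are infusions with a hospital stay of about 24 h or about 12 h. The third is "Oral treatment (by swallowing), and no hospital stay is required".
- **Extreme tiredness** (10%, 40%, 60%) and **hair loss** (none, thinning, complete) carry the same sentence: "It lasts as long as the treatment takes to be administered".
- **Skin problems** have a duration of their own, at least a month, with no reference to administration.

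The same section sets the standard: "attributes should be unambiguous, clear, tradable, and distinctly different from other included attributes". It drops activities of daily living partly because that item overlapped with other attributes and could be interpreted differently by different patients. It adds that the DCE and SW use the same attributes and levels so that they can be compared.

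Under DCE and SW Task Construction, the example DCE task (Table 3) shows mode as "Intravenous infusion lasting 24 h" against a 12 h infusion, and the SW example (Table 4) swings from a 24 h infusion to a pill. The interactions included in the design are survival with tiredness, survival with skin problems, and survival with mode.

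**The concern.** Treatment duration appears in Table 2 only in the mode attribute. A respondent who looks for how long tiredness or hair loss lasts is referred to the time of administration, and the only such time in the profile is 24 h, 12 h or a pill. Another respondent will take the sentence to mean for as long as therapy continues. These are very different burdens, and nothing described in the article would show the analyst which one a respondent had in mind.

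Three outputs are exposed:

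- the relative weights of mode, tiredness and hair loss, which are three of the five attributes;
- the MAR for tiredness, one of only two attributes expressed as a probability of harm, where MAR is a clinical endpoint;
- the comparison of DCE with SW, a methodological endpoint. SW values each improvement from the worst level, and for mode that is 24 h. The DCE averages over the mode levels shown.

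A second, smaller wording problem concerns mode itself. A stay in hospital and the running time of an infusion are different burdens, and the definition and the example tasks do not describe the same one.

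**Working it through.** There is no stated figure to reproduce, because the point concerns definitions. The first two steps set the text side by side. The third shows the direction of the consequence under assumed weights.

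**1. The two readings of the duration sentence**

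| Mode level shown | Single-administration reading | Whole-course reading |
|---|---|---|
| Infusion, about 24 h | about 24 h | the course |
| Infusion, about 12 h | about 12 h | the course |
| Oral | close to zero | the course |

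On the first reading the duration changes with mode; on the second, Table 2 gives no mode-specific duration. The skin-problem row shows that a duration can be stated without reference to administration. None of the three listed interactions is mode by tiredness or mode by hair loss.

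**2. The mode wording**

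| Place | Burden described |
|---|---|
| Table 2 | infusion with a hospital stay of about 24 h or 12 h |
| Table 3 | infusion lasting 24 h or 12 h |
| Table 4 | infusion lasting 24 h, improved to a pill |

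**3. Direction of the effect**

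All weights below are assumptions; none comes from the documents. Respondents have no intrinsic preference for mode:

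U = 0.5 × survival/10 − 0.2 × skin/10 − w × 0.4 × tiredness/10 − w × 1.2 × h

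Here h = 0, 0.5, 1 for no, thinning and complete hair loss. On the single-administration reading w = 1, 0.5, 0 for 24 h, 12 h and oral. On the fixed-duration reading w = 0.5 throughout.

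*Mode, by hand, single-administration reading.* Mean tiredness is (10 + 40 + 60)/3 = 36.7, costing 0.4 × 3.67 = 1.47. Mean hair loss costs 1.2 × 0.5 = 0.60. Oral against 24 h therefore appears worth 1.47 + 0.60 = 2.07, and 12 h against 24 h half of that, 1.03, although mode has no value of its own.

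*Mode, by simulation.* A conditional logit was fitted to random pairs with 510 × 12 × 20 = 122,400 choices. The number is large so that bias and not noise is visible.

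| Duration | Model | 12 h vs 24 h | Oral vs 24 h | Tiredness 60% to 10% |
|---|---|---|---|---|
| Fixed | listed interactions | 0.02 | 0.03 | 0.99 |
| Tied to mode | listed interactions | 0.91 | 1.94 | 0.94 (one average) |
| Tied to mode | plus mode × tiredness and mode × hair loss | −0.03 | 0.03 | 1.97 at 24 h, 0.98 at 12 h, 0.03 oral |

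*Tiredness MAR for survival 10% to 20%.* The gain is 0.5, and each 10 points of tiredness cost 0.4w, so MAR = 10 × 0.5/(0.4w) = 12.5/w points. That is 12.5 points at 24 h, 25 at 12 h, and unbounded for oral. A single reported value would hide this.

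*DCE against SW.* The tiredness swing is worth 0.4 × 5 × w = 2.0w, and the survival swing 0.5 × 3 = 1.5. If an SW respondent judges each swing with the other attributes at their worst level, w = 1 and the ratio is 2.0/1.5 = 1.33. A DCE average over the three modes in equal shares has w = 0.5 and a ratio of 1.0/1.5 = 0.67. The two methods would then differ without any difference in preference.

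*Share of literal readers.* If a share p reads the sentence as one administration, the average apparent value of oral against 24 h is about 2.07p: 0 at p = 0, 1.03 at p = 0.5, 2.07 at p = 1. The documents give no information on p.

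**The case against.** The strongest reply is that the whole-course reading is the natural one. Elsewhere in Table 2, starting treatment refers to the therapy as a whole, and hair loss lasting half a day makes little clinical sense. This stands as far as it goes: the sentence does not contain the word only, and it cannot be said that Table 2 fixes the duration at one administration. But the definition of mode uses treatment time in a per-session sense a few rows earlier, so the ambiguity is in the text.

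A second reply is that respondents read Italian or Dutch, see a video explaining the attributes, and that a think-aloud pretest with five patients precedes launch. That is fair. The survey text is not shown and may be clearer than the article. The pretest is the right place to find out, provided that duration is asked about.

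A reader might also infer stronger points that the documents do not support:

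- **That the attributes are statistically confounded.** The D-efficient design treats mode, tiredness and hair loss as separate attributes. The design matrix is not shown, and nothing indicates aliasing.
- **That the Introduction contradicts Table 2** because it gives infusion times of 4–5 h and about 1 h. Those are infusion times of existing therapies, whereas Table 2 gives hospital stays for hypothetical ones.
- **That one third of profiles show oral treatment.** This assumes level balance, which neither D-efficiency nor the removal of dominant pairs guarantees.
- **That mode interactions are excluded from the analysis.** Statistical Analyses leaves the final model open until the data are explored.

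**Conclusion.** The point holds as an ambiguity in attribute wording. One of two plausible readings makes the duration of tiredness and hair loss depend on the mode level, which would act as a mode-by-tiredness and a mode-by-hair-loss interaction that is not among those listed for the design. This falls short of the protocol's own criterion for attributes. It may distort the weights of mode, tiredness and hair loss, the MAR for tiredness and the DCE–SW comparison.

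The size cannot be determined. The apparent mode effect of about 1.9 logits rests on invented weights, random pairs, no intrinsic mode preference and every respondent reading literally; it shows direction only. If all respondents read the sentence as the whole course, this effect vanishes. The hospital-stay and infusion-length wording is a separate, smaller inconsistency that needs reconciling whichever reading applies. Both are worth correcting before launch because the correction is cheap and the analysis cannot recover what respondents understood.

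**What to change.** **Before launch**

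1. Reword the duration of tiredness and of hair loss as one stated period that does not depend on the mode level. The study team, with its clinicians, should set the wording.
2. Reconcile the hospital-stay and infusion-length descriptions of mode, and use one version in Table 2, the attribute video, the DCE tasks and the SW tasks, in both languages.
3. In the planned think-aloud interviews, ask patients how long they take tiredness and hair loss to last under each mode.

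The cost is text edits to the survey and one video, and possibly a minor ethics notification. The pretest is already planned and needs only an added question.

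**If the survey is already fielded**

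Report the ambiguity as a limitation on the mode, tiredness and hair-loss weights, on the MAR for tiredness, and on the DCE–SW comparison. Fit mode-by-tiredness and mode-by-hair-loss terms only as an exploratory DCE sensitivity analysis. They may be imprecise, since the design does not list them; they cannot separate respondents who read the sentence one way from those who read it the other; and they do nothing for SW.
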